#### Decisional conflict

Decisional conflict is measured using the Decisional Conflict Scale (DCS) [51, 60]. It comprises five subscales with a total of 16 items, which are assessed on a 5-point Likert scale (from 1 = strongly agree to 5 = strongly disagree). The subscales concern the following topics: being informed, clarification of personal values, support or pressure from others, uncertainty about the decision and the assessment of one’s own decision-making. The German version of the DCS has been shown to have good psychometric properties, with a reported internal consistency of Cronbach’s alpha = 0.78 or higher [60]. The DCS is administered at t0, t1 and t2.

#### Stage of decision-making

The stage of decision-making is measured using the Stage of Decision Making Scale (SDM-S) [52]. It consists of a single item with four or six response categories. In this study, an adapted German version with a four-answer category is used [61]. The categories used are (1) ‘I have not yet thought about the options’, (2) ‘I am considering the options’, (3) ‘I am close to choosing one option’ and (4) ‘I have already made a choice’. The SDM-S is administered at t0, t1 and t2.

#### Anxiety and depressive symptoms

To measure the symptoms of anxiety and depression, the German version of the Hospital Anxiety and Depression Scale (HADS-D) [53, 54] is used. It measures the level of anxiety and depressive symptoms in the last week by self-assessment. The HADS-D consists of two subscales (anxiety, depression) with seven items each, which are assessed on a 4-point Likert scale. The tool is widely used and shows good psychometric properties, with most studies reporting an internal consistency of Cronbach’s alpha = 0.8 or higher. It has been shown to be well suited for measuring emotional stress in cancer patients [62]. The HADS-D is administered at t0, t1 and t2.

#### Subjective stress symptoms because of the genetic test result

To determine the impact of the genetic test result of having a pathogenic *BRCA1/2* mutation on subjective stress symptoms the German version of the Impact of Event Scale-Revised (IES-R) is used [63]. The IES-R contains a total of 22 items in three subscales referred to as intrusion, avoidance and hyperarousal. They are assessed using a 4-point Likert scale (from 0 = not at all to 5 = often). The values of the three subscales can be used to calculate the probability of diagnosing a post-traumatic stress disorder. The IES-R is administered at t0 and t1.

#### Knowledge on cancer risks and preventive options

Knowledge about cancer risks associated with the *BRCA1/2* mutations and the available preventive options conveyed by the present DAs will be tested with a set of fifteen statements that can be classified as ‘true’, ‘not true’ or ‘don’t know’. In preparation for this study, this instrument was developed by a team of medical experts, psychologists and healthcare researchers working in the field of hereditary breast and ovarian cancer (HBOC). The topics covered by this instrument are addressed in the DAs and distributed as follows: four items each deal with the risks of BC/OC and risk-reducing breast surgery, three items each deal with the intensified breast cancer screening (and aftercare) programme and with risk-reducing adnexal surgery. One item concerns a topic that is explained in a section addressing ‘questions and answers’ of the DAs. Women’s level of knowledge is assessed at t0 and t1.

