### Baseline data collection at t0

After enrolment, all participants receive a package with study material (enrolment package). It contains the baseline questionnaire (t0) with a pre-stamped return envelope, brief and detailed information about the study and a copy of the informed consent document. Participants are invited to fill out the questionnaire at home and to return it within 2 weeks per regular mail.

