### Intervention

Once the completed baseline questionnaires (t0) have been returned to the data evaluation institution, the DAs will be sent by regular mail to those participants randomised to the IG with a request to use the DA for information and decision support at home. Previvors will receive DA-A, and survivors will receive DA-B.

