### Outcome data collections at t1 and t2

Participants, who have returned the baseline questionnaire (t0), will receive the follow-up questionnaire at t1 at 3-month-follow-up with the request to return the completed questionnaire within two weeks by regular mail. Participants who have returned the questionnaire t1 will receive the next follow-up questionnaire at t2 at 6-month follow-up with the request to return the completed questionnaire within two weeks by regular mail.

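### Knowledge at t1 is tested by post with aid-aligned items while only the intervention arm holds the aid, and nothing recorded can separate looking up answers from knowing them

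*Protocol article*

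**What the plan says.** All references are to the protocol article.

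- **Content of the test.** Under *Knowledge on cancer risks and preventive options*, the target is knowledge of cancer risks and "the available preventive options conveyed by the present DAs will be tested with a set of fifteen statements". On content, "The topics covered by this instrument are addressed in the DAs". For the last item, "One item concerns a topic that is explained in a section addressing" questions and answers in the aids. On authorship, "this instrument was developed by a team of medical experts, psychologists and healthcare researchers" in the field.
- **Timing.** Women's "level of knowledge is assessed at t0 and t1". *Outcomes {12}* lists change in knowledge among the secondary outcomes at t1.
- **Who has the aid, and when.** *Intervention {11a}* and *Intervention* send the brochure only to the intervention group, once the t0 form is back, "with a request to use the DA for information and decision support at home". *Promoting participant retention {18b}* lets controls request it only after t2.
- **How the forms are completed.** For t0, "Participants are invited to fill out the questionnaire at home". For t1, women who returned t0 "will receive the follow-up questionnaire at t1 at 3-month-follow-up with the request to return the completed questionnaire within two weeks by regular mail".
- **What controls hold.** *Choice of comparators {6b}* gives every woman a physician's letter and allows for further written information.
- **What is not recorded.** The *Discussion* says that, to avoid putting pressure on women, the t1 form does not ask about use of the aid. The limitations listed there cover non-use, contamination, unblinding and non-response, but not look-up of answers.

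**The concern.** Three features act together. The items are aligned with the aid. Women meet them at t0, before the aid arrives, so those who later receive it know what to look for. They meet them again at t1 in a mailed form, apparently unsupervised, when one arm has the aligned brochure to hand. A higher intervention-arm score could then come from better knowledge, from consulting the brochure while answering, or from both. The t1 form collects nothing that would separate these.

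At stake is the interpretation of one secondary outcome. *Objectives {7}* names knowledge-related effectiveness as part of the aim. The *Discussion* asks whether the aids improve knowledge and plans to bring them into routine care afterwards. A reported knowledge gain is likely to be cited in support, so readers need to know what it measures.

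**Working it through.** **1. Opportunity to look up answers at t1, by arm**

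| | Intervention | Control |
|---|---|---|
| Saw the statements at t0 | yes | yes |
| Physician's letter | yes | yes |
| Further written information | possible | possible |
| Decision-aid brochure at t1 | yes | no (on request after t2) |
| t1 mailed, two weeks to return | yes | yes |
| Asked at t1 about use of the aid | no | not applicable |

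The arms differ in one row, the brochure. That is the document the items are stated to match.

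**2. How far the letter overlaps with the test**

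Item counts from the knowledge section: breast and ovarian cancer risks 4, breast surgery 4, screening 3, adnexal surgery 3, questions-and-answers topic 1.

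4 + 4 + 3 + 3 = 14, and 14 + 1 = 15, as stated.

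*Choice of comparators {6b}* lists individual breast and ovarian cancer risks, the screening programme, and surgery of the breasts and of the ovaries and tubes as contents of the letter. At topic level the letter therefore touches the groups holding 14 of the 15 items. Whether it answers each statement cannot be seen from the article.

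**3. Group size used for illustration**

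*Sample size {14}* gives 139 per group for the primary outcome. This reproduces: a one-sided t-test with d = 0.3, α = 0.05 and power 0.80 needs 138.07, rounded up to 139. Then 139 / 0.90 = 154.4, rounded up to 155 per group and 310 in total. The point does not depend on this figure, which only sets n below.

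**4. What look-up alone could produce**

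The article gives no knowledge mean, SD or look-up rate, so these are assumptions: mean 10 of 15, SD 3 (held fixed), and look-up raises a woman's score to 14, a gain of 4 items. Let f be the share looking up in the intervention arm minus the share in controls.

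Spurious difference = 4f, and d = 4f / 3. The last column is the chance of a significant two-sided 5% t-test with 139 per group and no true gain.

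| Net share f | Difference (items) | d | Chance of significance |
|---|---|---|---|
| 5% | 0.2 | 0.07 | 0.09 |
| 10% | 0.4 | 0.13 | 0.20 |
| 15% | 0.6 | 0.20 | 0.38 |
| 20% | 0.8 | 0.27 | 0.60 |
| 30% | 1.2 | 0.40 | 0.91 |

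If 10%, 20% or 30% of intervention women look up and controls do so half as often, the net shares are 5%, 10% and 15%. The chances fall from 0.20, 0.60 and 0.91 to 0.09, 0.20 and 0.38.

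**5. Other assumptions**

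Suppose instead that look-up yields all 15 correct, 50% to 70% of items are otherwise correct, and the SD is 2 to 3. Then the difference is 15f(1 − p), where p is the proportion otherwise correct.

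- f = 10%: 15 × 0.10 × 0.30 = 0.45 to 15 × 0.10 × 0.50 = 0.75 items; d = 0.45/3 = 0.15 to 0.75/2 = 0.38; chance 0.24 to 0.88.
- f = 20%: 0.9 to 1.5 items; d = 0.30 to 0.75; chance 0.70 to nearly 1.

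The spread shows that the assumptions drive the result. These figures show sensitivity and do not predict the bias.

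**The case against.** The strongest reply has four parts.

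*Questionnaire instructions belong to the forms, which an article does not reproduce.* This stands in part. The missing closed-book instruction is not itself a finding, and one may exist. A reader might infer that t1 is an open-book test done at home, but the documents do not say so: completion at home is stated for t0, and for t1 only postal return is described. What remains is that the article itself fixes that t1 does not ask about use of the aid. That is a stated choice, not a detail left to another document.

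*Controls can look things up too.* This stands. A reader might infer that only the intervention arm can exploit having seen the items, or that the items are foreign to standard care. Neither is supported. Controls see the same t0 items, hold a letter on overlapping topics and may hold further written information. Nothing says the letter was not a basis for the items, and an expert team wrote them. The asymmetry is one of degree.

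*Testing what an aid conveys is legitimate.* This also stands. Alignment with the aid is not an error in itself. The weakness lies in repeating the test by mail with the aligned source available to one arm and no record of look-up.

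*The numbers are assumed.* They are, and they are labelled so. The direction of the concern follows from the design, but its size cannot be derived from the article.

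**Conclusion.** The point holds as a limit on interpreting one secondary outcome. Aligned items, a mailed repeat at t1, a brochure held by one arm only, and a deliberate decision not to ask about its use mean that part of a between-arm knowledge difference could be look-up, and the trial could not identify it.

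The size is unknown. With an assumed gain of 4 items and SD 3, a net excess of 5% to 20% of intervention women looking up answers corresponds to d of 0.07 to 0.27 and a 9% to 60% chance of a significant difference with no true gain. This also rests on two inferences: that the same statements are used at t0 and t1 (the article describes a single set assessed at both), and that t1 is completed unsupervised.

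A reader might conclude that the trial cannot support any claim that the aids improve knowledge. The documents do not go that far: a difference may well include real learning, and what is called for is a safeguard where one is still possible and cautious wording otherwise. The primary decisional-conflict result and its sample size are not affected.

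**What to change.** 1. **Where t1 forms are still to be sent**, in both arms: ask women to answer the knowledge items without consulting written material, and add one neutral tick box, *I looked something up*. It concerns behaviour during the test in either arm rather than use of the aid, so it need not create the pressure the authors wanted to avoid.
2. **Main score:** keep all 15 items. Restricting the claim to shared items would discard any knowledge the aid adds.
3. **Sensitivity analysis:** before unblinding, classify each item as covered by the standard physician's letter or covered only in the aid, and report the between-arm difference for each set.
4. **Where t1 forms are already collected:** do the item split and state possible look-up as a limitation of the knowledge claim. *Trial status* gives recruitment as closed on 30 September 2021, so this may be all that remains for many or all women.

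Cost: one instruction line, one extra tick box and a short item classification. The subset scores rest on fewer items and are less reliable, especially if few items prove to be covered only in the aid. The tick box relies on self-report and may undercount look-up.

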#### Preparation for decision-making

The German version of the Preparation for Decision Making Scale (PrepDMS) [57, 64, 65] will be used to measure the extent to which the participants feel prepared for the decision by the additional DA. The instrument consists of the two subscales ‘preparation for the decision’ and ‘preparation for the physician’s consultation’ and comprises a total of ten items, which are rated on a 5-point Likert scale (from 1 = not at all to 5 = a great deal). This instrument is validated, shows good internal consistency (Cronbach’s alpha = 0.95 for total score) and is recommended for the evaluation of DAs [65]. The PrepDMS is administered at t1.

#### Acceptability

Acceptability of the DAs among participants of the IG is measured by an acceptability scale. Participants of the CG will judge the written information received as part of standard care with the same instrument. The tool is adapted from an acceptability tool developed by O’Connor and Cranney [58] and from an approach to test acceptability described in a study by Metcalfe et al. [30]. It consists of seven items in which personal assessments of the following characteristics of the received DA are queried: (1) scope, (2) amount of information, (3) comprehensibility, (4) usefulness in making a decision on a preventive measure, (5) satisfaction with the DA, (6) sufficient information to make an appropriate decision and (7) likelihood of recommending the DA to other women in her situation. Items (1), (2), (6) and (7) are assessed with a dichotomous response format; items (3), (4) and (5) are scored with a 3-step ordinal response format. The acceptability scale is administered at t1.

#### Decision regret

To assess the participants’ level of distress and regret in terms of the final decision made, the Decision Regret Scale (DRS) [21, 59, 66] is used. It consists of five items to be rated on a 5-point Likert scale (from 1 = strongly agree to 5= strongly disagree). The instrument was validated in a sample of BC patients and showed good internal consistency with a Cronbach’s alpha = 0.81 to 0.92. It is strongly negatively correlated with decision satisfaction and overall quality of life and positively correlated with decisional conflicts [21]. The DRS is administered at t2.

The outcome parameters and time points for outcome measurements are listed in Table 1.

### Participant timeline {13}

The schematic participant timeline is shown in Fig. 1.

**Fig. 1 Fig1:**
[figure not shown]
Participant timeline

### Enrolment and randomisation

Recruitment takes place during a specialist consultation either (1) directly following the post-test genetic counselling or (2) during a medical examination as part of the intensified breast cancer screening programme (for previvors, A) or the intensified breast cancer screening and aftercare programme (for survivors, B). If the inclusion criteria are met, eligible women will be informed about the study and invited to participate. Women who agree to do so will be asked to provide informed consent. Physicians will complete a recruitment form. Thereafter, participants are randomly assigned to one of the two study groups. The allocation is blinded to both the recruiting physicians and the participants.

### Baseline data collection at t0

After enrolment, all participants receive a package with study material (enrolment package). It contains the baseline questionnaire (t0) with a pre-stamped return envelope, brief and detailed information about the study and a copy of the informed consent document. Participants are invited to fill out the questionnaire at home and to return it within 2 weeks per regular mail.

### Intervention

Once the completed baseline questionnaires (t0) have been returned to the data evaluation institution, the DAs will be sent by regular mail to those participants randomised to the IG with a request to use the DA for information and decision support at home. Previvors will receive DA-A, and survivors will receive DA-B.

### Outcome data collections at t1 and t2

Participants, who have returned the baseline questionnaire (t0), will receive the follow-up questionnaire at t1 at 3-month-follow-up with the request to return the completed questionnaire within two weeks by regular mail. Participants who have returned the questionnaire t1 will receive the next follow-up questionnaire at t2 at 6-month follow-up with the request to return the completed questionnaire within two weeks by regular mail.

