#### Intervention {11a}

Participants in the IG will also receive standard care as described above. After the return of the baseline questionnaire (t0), participants of the IG will be sent the DAs as a brochure by regular mail. Participants of the CG will not receive a DA.

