### Definition of analysis population {20c}

All analyses will be conducted following the intention-to-treat (ITT) principle including all randomised patients. No imputation of missing values will be performed.

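### The t2 questionnaire goes to women who returned t1, so every t2 comparison is restricted by design to t1 responders, a set that may differ by arm

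*Protocol article*

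**What the plan says.** The protocol article, under Outcome data collections at t1 and t2, sets a chain of two conditions. For the first follow-up: "Participants, who have returned the baseline questionnaire (t0), will receive the follow-up questionnaire at t1 at 3-month-follow-up". For the second: "Participants who have returned the questionnaire t1 will receive the next follow-up questionnaire at t2 at 6-month follow-up". The word 'only' does not appear, but that is the plain reading, and no other section sends t2 to a woman whose t1 did not come back.

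The sections that bear on this rule are:

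- **Outcomes {12}** lists the t2 outcomes: stage of decision-making (SDM-S), decisional conflict (DCS), anxiety and depression (HADS) and decision regret (DRS). Regret is measured at t2 alone and is one of the hypotheses under Objectives {7}.
- **Unblinding {17b}** states that intervention women know their arm once the decision aid arrives, and control women once t1 arrives without one.
- **Promoting participant retention and complete follow-up {18b}** says that control women may be likelier to drop out. It provides postal reminders and a telephone call for late questionnaires, and offers control women the decision aid once t2 is returned.
- **Definition of analysis population {20c}** states: "All analyses will be conducted following the intention-to-treat (ITT) principle including all randomised patients", followed by "No imputation of missing values will be performed".

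**The concern.** Missing one questionnaire is not withdrawal. Under Criteria for discontinuing or modifying allocated interventions {11b} and Additional consent provisions {26b}, leaving the study is a separate act by the participant. The sending rule nevertheless treats one missed mailing as the end of follow-up.

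Because t1 response follows randomisation and unblinding, the women who can contribute to t2 are selected by something that may depend on the arm. If response also relates to how a woman is coping with her decision, the t2 comparison no longer has the full protection of randomisation. Decision regret is the most exposed outcome: it has no t0 or t1 measurement, so women without t2 contribute nothing to it. The plan does not impute, so nothing in the document corrects for the selection.

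**Working it through.** **Step 1: who can have t2 data.** Read together, the sections give this path:

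1. Consent and enrolment, then: "Thereafter, participants are randomly assigned to one of the two study groups".
2. t0 is mailed back while participants are still blinded (Blinding {17a}).
3. Intervention women receive the decision aid after t0 is returned.
4. t1 goes to t0 returners. Both arms know their allocation by the time they answer.
5. t2 goes to t1 returners.

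The condition between steps 4 and 5 is the one at issue. It acts after randomisation and unblinding, and it affects t2 outcomes only. The primary outcome, the change in DCS at t1, is already fixed when it acts.

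**Step 2: the plan's own numbers.** Sample size {14} uses d = 0.3, α = 0.05, a one-sided t-test and power 0.80 (printed as β). The exact t-test calculation gives 138.07, rounded up to 139 per group. With 10% drop-out, 139 / 0.90 = 154.4, rounded up to 155 per group, or 310 in total. The stated figures reproduce and are not in dispute. They supply only the starting number of 310.

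**Step 3: illustrative loss at t2.** The document gives no return rate per mailing, so let p be an assumed common rate, and r the assumed share of t1 non-returners who would answer t2 if asked.

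- With the rule: 310 × p³
- Without it, if t1 non-returners answer as often as everyone else (upper bound): 310 × p²
- Without it, at share r: 310 × p × [p² + (1 − p) × r]

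| p | With the rule | r = 25% | r = 75% | Upper bound |
|---|---|---|---|---|
| 95% | 266 | 269 | 277 | 280 |
| 90% | 226 | 233 | 247 | 251 |
| 85% | 190 | 200 | 220 | 224 |

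Worked at p = 0.90:

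- With the rule: 310 × 0.729 = 226.0, which is 73% of 310.
- Upper bound: 310 × 0.81 = 251.1.
- r = 0.25: 279 × (0.81 + 0.025) = 233.0.
- r = 0.75: 279 × (0.81 + 0.075) = 246.9.

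The women lost through the rule itself therefore number about 7 to 21 at 90% return, 4 to 11 at 95% and 10 to 30 at 85%. The remaining loss at t2 is ordinary non-response, which would occur anyway.

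**Step 4: bias.** Its size and direction would need the t1 return rate by arm and the relation between t1 return and t2 outcomes. The document gives neither, so no figure can be computed.

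**The case against.** The strongest reply is that the exposure is limited and largely acknowledged. All t2 outcomes are secondary. Late returners get up to two postal reminders and then a telephone call, so a woman who still has not returned t1 may well ignore t2 too. Control women have an incentive to stay, since they may request the decision aid after t2. The Discussion openly lists bias from non-response, especially if it differs by arm.

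Most of this stands as a limit on size, and it is why the counts without the rule are given as a range below the upper bound. It does not remove the rule. Reminders chase a questionnaire that was sent; they do not send t2 to someone who missed t1. The incentive rewards returning t1, but a control woman who misses t1 is never sent the questionnaire on which the offer depends. The Discussion treats non-response as unavoidable and does not mention that part of it is created by the mailing rule.

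A reader might be tempted to go further in four ways that the document does not support:

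- **That the primary outcome or its power is at risk.** The t1-to-t2 rule acts after the primary outcome is collected. Whether enough women return t0 and t1 is a separate sample-size question, and mailing t2 more widely would not change it.
- **That lost t2 values weaken the primary analysis by no longer informing missing t1 values.** The primary test is a t-test without imputation, so t2 values would not be used for it in any case.
- **That the condition on t0 return biases the comparison in the same way.** "Participants, who have returned the baseline questionnaire (t0), will receive the follow-up questionnaire at t1" does leave some randomised women without follow-up. But t0 is answered blinded, so non-return should not select by arm, and a change score needs t0 anyway.
- **That the protocol predicts higher control drop-out.** It says only that this is possible, and it sets out a countermeasure.

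**Conclusion.** The point holds for the t2 outcomes. As written, DCS, SDM-S, HADS and decision regret at six months are compared only among women who returned t1. That set is formed after randomisation and unblinding, at a stage where the protocol itself regards unequal drop-out as possible. This fits poorly with analysing all randomised women by intention to treat, and the selection is avoidable.

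The conclusion rests on the plain reading of the sending rule. The bias cannot be quantified from the document. The loss of data is modest: at an assumed 90% return per mailing, about 226 of 310 women with t2 data, against about 233 to 247 without the rule and at most about 251. These counts assume one return rate for all mailings and both arms. The point does not touch the primary outcome at t1. It is a cheap improvement to the secondary t2 comparisons and does not threaten the trial's main conclusion.

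**What to change.** Amend Outcome data collections at t1 and t2 so that the t2 questionnaire, with the usual reminders and telephone call, goes to every woman who returned t0 and has not withdrawn consent, whether or not t1 came back.

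Trial status gives recruitment as closed on 30 September 2021, so the change can reach only women who have not yet passed six months when it takes effect. For women already past that point, report the t2 results explicitly as conditional on t1 response.

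There is no reason to move the point of randomisation. The decision aid is already dispatched only after t0 is returned, and with recruitment closed such a change would come too late.

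The cost is a short amendment, which under Protocol amendments {25} needs ethics approval before use, plus some extra mailings and reminders. Over a whole trial of 310, the extra t2 questionnaires would number 310 × p × (1 − p): about 15 at 95% return, 28 at 90% and 40 at 85%. Fewer would be needed now, since some women will already have passed six months.
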